##### Primary Outcome

For the primary outcome (sleep efficiency based on actigraphy and sleep diary data), we will test for a significant interaction effect between time and group, which would indicate differential rate of change over time between groups. Differences in the estimated means between the intervention group and usual care group will also be compared at the 4-month post treatment time point (primary end point) to determine the magnitude of differences between groups [114].

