#### Primary Objective and Hypothesis

The primary objective is to assess the *immediate impact* (baseline vs 4 months) of the intervention on children’s sleep.

We hypothesize that at the end of the 4-month assessment period, children randomized to the intervention group will evidence improvement in their symptoms of insomnia compared with children in the usual care group. The outcome variables are sleep efficiency collected by both an objective measure (actigraphy) and a parent report measure (sleep diary).

There are 2 hypotheses for the primary outcome:

We hypothesize that children in the intervention group will show improvements in sleep efficiency calculated using *actigraphy* data compared with the usual care group.We hypothesize that children in the intervention group will show improvements in sleep efficiency calculated using *sleep diary* data compared with the usual care group.

Note that sleep efficiency is a measure that captures both sleep quantity and quality and is defined as the amount of total sleep time divided by the amount of time spent in bed with the goal to be sleeping. For example, if a child went to bed at 8 PM and woke at 8 AM, but took 1 hour to fall asleep and was awake for 30 min throughout the night, the child’s sleep efficiency would be 87.5% (ie, (630 min/720 min) × 100).

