### Statistical Analysis

#### Sample Size Analysis

A total goal of 500 consented participants is expected. Using the assumption that 50.0% (250/500) of participants will be lost to follow-up, the target sample size at the end of the study is n=250 [107-109]. This gives us power of .80 to detect a significant group-by-time interaction with the effect size (*d*)=0.45 and alpha set to .025, for primary outcome measures calculated from actigraphy and sleep diary from baseline to 4-month follow-up. Given that 2 primary outcome variables are being used (sleep efficiency from actigraphy and sleep efficiency from sleep diaries), alpha was divided by 2 so that *P*=.025, rather than *P*=.05 would be accepted as indication of statistical significance. This is based on the assumption that an effect size of *d*=0.45 is clinically significant for sleep efficiency as measured by actigraphy and sleep diary [45].

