#### Data Analysis

The primary outcome variables that will be used to evaluate the impact of the intervention program on insomnia symptoms are sleep efficiency from actigraphy and sleep efficiency from sleep diary data. Overall, 2 primary outcome measures are included to capture these variables of interest using both an objective measure of sleep (ie, actigraphy) and a parent report/subjective measure of sleep (ie, sleep diary), thus allowing us to compare our results with existing research in the field. In unblinded RCTs (ie, in which participants know their group assignment such as this study), there is evidence of bias toward significance of the active treatment; thus, an objective measure (eg, actigraphy) is used to mitigate this bias [110]. However, as parents are the primary decision makers with respect to seeking treatment for their child’s health problems, it is also critical to obtain their perspective. Further, inclusion of patient-reported outcomes is recommended when testing interventions [111].

Secondary outcomes for this study examine the maintenance of changes in sleep, as well as the impact on the child’s psychosocial health (behavioral, attentional, and emotional functioning) and on parents’ psychosocial health (ie, psychological adjustment). Data analyses are overseen by the research team, including the statistician, using an intent-to-treat data analytic approach [112].

Conditional growth model methodology, also known as hierarchical models, a generalization of the standard linear model, which permits data to exhibit correlation and nonconstant variability, will be used to fit each outcome at baseline, 4 months, and 8 months [113] using PROC MIXED in the Statistical Analysis System. Model formulation is at 2 levels, with participants as level 1, and treatment group as level 2. The level 1 model is a linear individual growth model, and the level 2 model expresses variation in parameters from the growth model as random effects unrelated to any person-level covariates. For each parent, the actual time (in days) from baseline to when each follow-up assessment is completed is also entered, to account for variation in when parents actually complete assessments.

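### The primary question and power are set at baseline to 4 months, but the model as written tests a straight-line slope over baseline, 4 and 8 months; the sections do not agree on which visits define the primary test

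*Protocol article*

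**What the plan says.** **Question.** Primary Objective and Hypothesis: "The primary objective is to assess the *immediate impact* (baseline vs 4 months) of the intervention on children’s sleep". Sleep efficiency at 8 months is placed under the secondary objectives.

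**Power.** Sample Size Analysis: "This gives us power of .80 to detect a significant group-by-time interaction with the effect size (*d*)=0.45 and alpha set to .025", and this is "for primary outcome measures calculated from actigraphy and sleep diary from baseline to 4-month follow-up". Half of 500 participants are assumed lost, leaving 250.

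**Model.** Data Analysis: growth models "will be used to fit each outcome at baseline, 4 months, and 8 months". On the shape of time: "The level 1 model is a linear individual growth model". The actual days from baseline to each follow-up are entered as well.

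**Test.** Primary Outcome: "we will test for a significant interaction effect between time and group, which would indicate differential rate of change over time between groups". The next sentence says that estimated means "will also be compared at the 4-month post treatment time point (primary end point) to determine the magnitude of differences between groups".

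**Secondary outcomes.** The Secondary Outcome section again uses a time-by-group interaction. There, but not in the Primary Outcome section, it says that all three assessments enter, and it gives the 8-month effect as the aim.

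**The concern.** With two visits, a group-by-time interaction in a linear model is the difference between arms in baseline-to-4-month change. With three visits and time as a straight line, it is a difference in slopes over the whole 8 months. The primary hypothesis concerns the first quantity; the model described under Data Analysis yields the second.

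The two agree only if the arms keep diverging at a constant rate up to month 8. The protocol does not describe that course. The recommended time to complete the program is 5 to 10 weeks, 4 months is called the end of treatment, and the later period is described as maintenance. A line fitted to a rise followed by a plateau misstates the 4-month difference. Where the effect changes after month 4, the slope test responds to that change and not only to the 4-month effect.

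**Working it through.** **Inputs from the protocol.** d = 0.45; alpha .025 for each outcome (sidedness not stated, two-sided assumed); 250 analysed with 1:1 allocation, so 125 per arm; follow-ups at 16 and 32 weeks after randomization, so nominal spacing 0, 16, 32. **Assumed:** unit SD at each visit and an equal correlation rho between visits. The article gives no rho, so .3, .5 and .7 are shown.

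**1. The stated power.** For the baseline-to-4-month change, SE = sqrt(2 × 2(1 − rho)/125) and power ≈ Φ(0.45/SE − 2.241).
- rho .3: SE = 0.150, power 0.78
- rho .5: SE = 0.126, power 0.91
- rho .7: SE = 0.098, power 0.99

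The stated 0.80 is reached at rho of about 0.33. The figure therefore fits a two-visit change contrast, but only with a correlation that the article does not state.

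**2. What the three-visit slope estimates.** With complete, equally spaced data, the slope scaled to 4 months has weights (−0.5, 0, +0.5) on the three visits. The fitted 4-month value has weights (1/3, 1/3, 1/3). Ordinary and generalized least squares give the same weights here.

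| True arm difference at 0, 4, 8 months | Slope × 4 months | Line's 4-month difference |
|---|---|---|
| 0, d, 2d (continued divergence) | 1.00d | 1.00d |
| 0, d, d (maintained) | 0.50d | 0.67d |
| 0, d, 0.5d (half fades) | 0.25d | 0.50d |
| 0, d, 0 (all fades) | 0 | 0.33d |
| 0, 0, d (8 months only) | 0.50d | 0.33d |

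**3. Power of the slope test, complete data.** The slope test is equivalent to testing the baseline-to-8-month change. Its SE is that of step 1, and the 8-month difference takes the place of 0.45.

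| True course | rho .3 | rho .5 | rho .7 |
|---|---|---|---|
| Maintained | 0.78 | 0.91 | 0.99 |
| Half fades | 0.23 | 0.32 | 0.52 |
| All fades | 0.025 | 0.025 | 0.025 |
| 8 months only | 0.78 | 0.91 | 0.99 |

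Example, half fades, rho .5: 0.225/0.126 − 2.241 = −0.46, and Φ(−0.46) = 0.32. The 4-month change contrast keeps 0.78/0.91/0.99 in the first three rows and falls to 0.025 in the last, where no 4-month effect exists.

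**4. With missing 8-month data.** Assume that all 125 per arm have baseline and month 4, that half of them miss month 8, and that nothing is imputed. Generalized least squares then gives month 4 some weight.
- Maintained: slope × 4 months is 0.59–0.60d and the line's 4-month difference 0.72–0.73d.
- Half fades: slope × 4 months is 0.38–0.39d; power 0.35/0.49/0.74.
- All fades: slope × 4 months is 0.17–0.19d.

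The attenuation is milder but does not go away.

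**The case against.** The best defence is that the article may intend a two-visit primary test. The Sample Size Analysis describes the interaction as running from baseline to 4 months. The Primary Outcome section does not list the visits and calls 4 months the primary end point. Three assessments are spelled out only for secondary outcomes. With two visits at nominal times, the linear slope is the 4-month contrast and none of the dilution above arises. The age-group analysis also lists time beside age group and arm, as one would list a factor, so the coding of time is not beyond doubt. This stands as far as it goes: one cannot say that the three-visit slope is settled as the primary test. But Data Analysis says that each outcome is fitted at all three visits with a linear model, and the Primary Outcome section makes no exception to that.

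Second, the protocol expects benefit to last, and under full maintenance with complete data the slope test loses no power against the unadjusted 4-month change. This stands. Loss of power needs fading, which is an assumption here. The bias in the 4-month difference does not need fading: it is present under the maintenance that the protocol expects, if those means come from the linear model.

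A reader might also infer two rival primary tests for each outcome at the same .025. The text does not support that: it gives the interaction the significance test and the 4-month means the role of showing magnitude, with no second alpha. Nor does it support a bias from a gap between baseline and randomization. The article gives no length for such a gap, and any gap comes before allocation.

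**Conclusion.** The point holds as an inconsistency with consequences. The objective and the power calculation concern baseline to 4 months, while the model and test, applied as written, give a slope that with complete data at nominal times puts no weight on month 4.

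Its size depends on the course after month 4. If the effect is maintained, the cost is a 4-month difference reported at 0.67d (0.72–0.73d if half of the children miss month 8), with equal power when data are complete. If half fades, power falls to 0.23/0.32/0.52 with complete data, or 0.35/0.49/0.74 with half missing month 8, against 0.78/0.91/0.99. An 8-month effect with no 4-month effect can also produce a significant primary result.

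These figures rest on assumed correlations, equal correlation between visits, nominal visit times and a two-sided test. It would go too far to conclude that the trial will miss a true 4-month benefit, since that requires fading that the protocol does not predict.

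**What to change.** In Data Analysis and Primary Outcome, model visit as categorical (baseline, 4 months, 8 months), or otherwise allow a non-linear time course. Name the between-arm contrast at 4 months as the single primary test for each of the two sleep-efficiency outcomes at .025. Make the month-8 contrast from the same model secondary. Actual assessment days may stay as a covariate or go to a sensitivity analysis.

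The cost is a wording change, a few lines of PROC MIXED code and one or two extra parameters. No new data are needed, and the test then matches the objective and the interval that was powered.

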##### Secondary Outcome

For the secondary outcomes, we will test differences between the 2 groups modeling changes in the outcome variables across the 3 points of measurement (baseline, 4 months, and 8 months postrandomization) to determine treatment effects at 8 months postrandomization. Again, a significant time × group interaction would indicate differential rate of change over time between groups. Differences in the estimated means at the 4-month and 8-month posttreatment time points will also be examined.

To examine the possibility of differential response to treatment across the 3 age groups, we will use a growth curve modeling of the 2 primary outcomes (sleep diary and actigraphy). Analysis is based on the methodology of the extension of the generalized linear model for longitudinal data, namely marginal and random effects modeling, which allows for varying intercepts and slopes across subjects, “G-side” random effects, and different within-person error variance covariance structure, “R-side” random effects [115,116]. An interaction of age group (toddler, preschool-aged, and school-aged) × time (3 assessments) × randomization group (intervention and usual care) would indicate differential response to treatment.

An intent-to-treat analysis will be conducted. Multiple imputation techniques will be used to deal with missing data. This method works well on longitudinal data and is robust to violations of non-normality of the variables used in the analysis.

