##### Actigraphy

An actigraph is a battery-operated device utilizing an accelerometer to detect motor activity. We use the Philips Respironics Actiwatch 2 (Koninklijke Philips N.V., Amsterdam, NL). When an actigraph is worn, a computer chip located inside the device records movement, which is used to determine a number of sleep variables, including but not limited to sleep efficiency (captured from lights out to awakening), sleep onset, total sleep time, and night waking [9,18].

Participants are asked to have their child wear the actigraph on their child’s wrist of their less dominate hand. Children 1 to 2 years of age wear the actigraph on their ankle. Participants are instructed to record any instances in which the actigraph is removed from their child’s body for any length of time. Participants are instructed to have their child wear the actigraph for 7 days, with a minimum requirement of 5 days.

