#### Randomization

After completion of baseline measures, participants are randomized. A blocked stratified randomization is used with 1-to-1 allocation for parents to either the intervention group or the usual care group. Participants are not blinded to their assignment group. Participants are stratified by age groups: toddler (1-2 years of age); preschool-aged (3-5 years of age); and school-aged (6-10 years of age). Blocks of 4 are used to randomize the participants for each stratum (ie, each age group).

The randomization table was created using the block random function in the R statistical software [106] and inputted into REDCap by a research staff member who is not associated with the management of participants. The only individuals who have access to the randomization table are not associated with participant management and include the research associate (EAB) who created the random allocation table based on the study design and a coinvestigator with extensive RCT design experience (RS) and the study statistician (PA), who reviewed the randomization table. The statistician conducting the primary analysis will be blinded to participant allocation to intervention or usual care groups (ie, the statistician will not be given the code for this variable).

Research staff members randomize participants using an automated REDCap procedure. The randomization table, created in Microsoft Excel, is uploaded into the REDCap database, where it cannot be modified or accessed. Only the research associate is able to view the randomization table. Once a participant completes baseline assessment, research staff members confirm all criteria are met and “trigger” the automated randomization by clicking a button within the program. An automated email is sent to participants to notify them of the randomization result.

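### For actigraphy, the toddler-versus-older part of the age interaction cannot tell a different treatment response from a different sensor responsiveness, because ankle wear coincides with the toddler stratum

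*Protocol article*

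**What the plan says.** Four statements in the protocol article bear on the point.

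- **Sensor site** (Measures, Actigraphy): the device goes on the "wrist of their less dominate hand", with one exception: "Children 1 to 2 years of age wear the actigraph on their ankle".
- **Strata** (Randomization): "Participants are stratified by age groups: toddler (1-2 years of age); preschool-aged (3-5 years of age); and school-aged (6-10 years of age". The Recruitment section uses the same three bands, with a target of 167 children in each.
- **Allocation** (Randomization): "Blocks of 4 are used to randomize the participants for each stratum (ie, each age group". Allocation is 1:1, so within each age group both arms follow the same site rule.
- **Moderation analysis** (Data Analysis, Secondary Outcome): to look for differential response by age, "we will use a growth curve modeling of the 2 primary outcomes (sleep diary and actigraphy"; and an interaction of age group and time with "randomization group (intervention and usual care) would indicate differential response to treatment". This reading is applied to both outcomes, without separating them and without mention of sensor site.

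**The concern.** The age at which the sensor moves from ankle to wrist is the age at which the toddler stratum ends. In the actigraphy data, every contrast between toddlers and older children is therefore also a contrast between two sensor sites, and no model fitted to these data can estimate the two separately.

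If an ankle sensor registers a given true change in wakefulness more weakly or more strongly than a wrist sensor, equal benefit at all ages would appear as an interaction, and a real age difference could be hidden. The stated inference, that an interaction indicates differential response, does not follow for this part of the actigraphy test.

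At stake is the objective half of the answer to which age group benefits, a question the trial has prepared for by stratifying on age and recruiting equal age groups.

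**Working it through.** The document gives no power or precision figure for the moderation analysis, so there is none to reproduce. The stated power of .80 concerns the primary group-by-time test and has no bearing here.

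**1. Is site fully aliased with stratum?** Take an intercept and two age-group dummies: the design has rank 3. Adding an ankle indicator leaves the rank at 3. Site is an exact function of stratum.

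**2. What happens to a constant site offset?** The tested quantity is a difference of differences in differences: (change in intervention − change in usual care) among toddlers, minus the same among older children. Adding a constant to all ankle readings shifts baseline and follow-up equally, so each child's change is untouched. Offsets of −10, −5 and +5 points of sleep efficiency each alter the contrast by exactly 0.

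**3. What happens to a difference in responsiveness?** Suppose ankle readings multiply true change by k. The documents give no value, so k is an assumption. Let the true effect be d = 0.45 SD at every age, the effect size in the Sample Size Analysis section. Toddlers then show 0.45k, older children 0.45, and the spurious contrast is (k − 1) × 0.45.

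**4. How often would that be declared significant?** Inputs: 250 analysed (Sample Size Analysis, after 50% loss), three equal strata, so n = 250/3 = 83.3 per stratum, split 1:1; change-score SD 1; two-sided .05 (assumed, as the article sets no level for this test).

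- Variance of the toddler effect: 4/83.3 = 0.048.
- Variance of the older-children effect: 4/166.7 = 0.024.
- SE of the contrast: √(0.048 + 0.024) = 0.268.
- With δ = |k − 1| × 0.45 / 0.268, the rejection probability is 1 − Φ(1.96 − δ) + Φ(−1.96 − δ).

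| k (assumed) | Spurious contrast (SD) | Rejection, toddler vs older (1 df) | Rejection, three-level age factor (2 df) |
|---|---|---|---|
| 0.9 | −0.045 | 5.3% | 5.2% |
| 0.8 | −0.090 | 6.3% | 5.9% |
| 0.7 | −0.135 | 7.9% | 7.0% |
| 0.5 | −0.225 | 13.4% | 10.7% |

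The 2-df column uses a noncentral chi-square with noncentrality δ². With time as three categories (4 df) the last two rows fall to 6.3% and 8.8%. If the toddlers' SD shrinks by k as well, the 1-df figures rise to 9.5% at k = 0.7 and 22% at k = 0.5.

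**5. How does this compare with the precision of the test?** The toddler-versus-older contrast detectable with 80% power is (1.96 + 0.84) × 0.268 ≈ 0.75 SD, well above any artefact in the table.

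**6. Does the site stay fixed within a child?** The article does not say what happens when a child turns 3 during follow-up. If entry ages are uniform over 12 to 36 months (assumption), the share of toddlers passing their third birthday by week 32 is 32/52.18/2 ≈ 31%. Were the site to follow current age, the offset would no longer cancel within those children. It would still balance between arms on average, because allocation is randomized within the stratum, but it would add noise and mix sites within the stratum.

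**The case against.** The strongest reply has four parts.

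*The test is protected by design.* Each child has a baseline and both arms of a stratum share a site, so an ankle–wrist offset drops out. This stands. A reader might infer from the shared age cut that any difference between sensor sites contaminates the age comparison, or that the treatment effect itself is in doubt. The documents support neither: only a difference in responsiveness to change matters, and the randomized comparison within each stratum is sound.

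*Nothing in the documents shows that k differs from 1.* This also stands. The article does not describe scoring settings, and it refers to an appendix on measures that is not shown, so a lack of site-specific scoring cannot be inferred. What the article does contain is an unconditional interpretation, and that is what is at issue.

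*The size is small and the analysis is weak anyway.* Largely right. At k = 0.7 the excess over nominal is about 3 percentage points, less for the omnibus test, and low power limits the analysis more than the artefact does. The bias in the estimated contrast is present, however, whether or not the test is significant.

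*The plan already holds cross-checks.* The same model is run on the diary, which has no sensor, and preschool versus school-aged is wrist against wrist. This is true, but the article does not tie the reading of the actigraphy interaction to either.

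**Conclusion.** The point holds in a limited form and is minor. For actigraphy, the toddler-versus-older component of the age by time by arm interaction is completely aliased with sensor site, so by itself it cannot be read as differential response to treatment.

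The alias follows from the text alone. The size of any bias does not: it rests on an assumed scaling factor k, a common true effect of 0.45 SD, unit change SD and 250 analysed. On those terms the spurious contrast is 0.135 SD at k = 0.7 and 0.225 SD at k = 0.5 in absolute value, falsely significant about 8% and 13% of the time as a 1-df contrast.

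The primary 4-month comparison, the diary interaction and the 3–5 versus 6–10 actigraphy contrast are not affected.

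**What to change.** In the Secondary Outcome part of the Data Analysis section, or in the SAP, replace the single reading of the actigraphy interaction with two pre-specified contrasts:

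- **Preschool versus school-aged**, both measured at the wrist. This can be read as differential response.
- **Toddler versus older**, reported as confounded with sensor site and presented beside the same contrast on the diary. It is not read as differential response on its own.

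The diary should serve as context, not as a strict gate: it is reported by unblinded parents, and the article relies on actigraphy to offset that bias. Dividing each stratum's effect by its own baseline SD is not advised, since real differences in SD between age groups would then create the same kind of artefact.

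Also state that the sensor site assigned at baseline is kept for each child at all assessments, or, if it was not, record the site at each assessment.

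The cost is a few sentences and no new data. The downside is a weaker actigraphy claim about toddlers.
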